## Abstract

**Background:**

Cognitive impairment is common in Parkinson’s disease (PD). Up to 80% of people with PD develop dementia over the disease course, heavily impacting their quality of life. While pharmacological treatment options are scarce, previous research highlights the potential benefits of non-pharmacological interventions, such as cognitive training (CT), on cognition and non-cognitive outcomes. This study’s purpose is to examine the feasibility as well as short- and long-term effects of a 5-week digital CT in people with advanced PD, compared to people with advanced PD receiving care as usual, and to explore possible predictors of CT responsiveness.

**Methods:**

This ongoing monocentric, two-armed randomized controlled trial (RCT) seeks to include 140 participants with advanced PD according to the established 5-2-1 criteria. Participants are randomized into either the experimental group, receiving a structured 5-week digital CT and additional psychoeducational videos on cognitive health, or a passive control group receiving care as usual. CT will be carried out remotely from home and supervised by the study team. Feasibility will be assessed using a training diary (e.g., motivation, satisfaction) and technical data (e.g., training duration). Neuropsychological assessments will be carried out pre- and post-CT and after a 3-month follow-up period. The primary outcome will be global cognition measured with the Montréal Cognitive Assessment (MoCA). Secondary outcomes include further cognitive, motor, and (neuro)psychological variables (e.g., quality of life, motor symptoms, mood, activities of daily living).

**Discussion:**

Studies on CT in people with PD have demonstrated positive effects on cognition, promoting the application of CT as a non-pharmacological treatment approach. However, studies targeting people in more advanced PD stages are rare or non-existent, despite it being a clinically relevant target group. Further, few studies have looked at long-term CT effects in PD, and very little data exists regarding CT predictors. Therefore, this large-cohort study of a multi-domain digital CT in people with advanced PD aims to provide insights into the effects, feasibility, and acceptability of CT within a representative sample of people with PD, allowing for statistically high-powered analyses and the identification of potential CT predictors.

**Trial registration:**

German Clinical Trials Register (DRKS) DRKS00028876. Registered on 21 November 2022

## Administrative information

Note: The numbers in curly brackets in this protocol refer to SPIRIT checklist item numbers. The order of the items has been modified to group similar items (see http://www.equator-network.org/reporting-guidelines/spirit-2013-statement-defining-standard-protocol-items-for-clinical-trials/).

## Introduction

### Background and rationale {6a}

Parkinson’s disease (PD) is one of the most common and fastest-growing neurodegenerative diseases [1–3]. In addition to its characteristic motor symptoms (bradykinesia, rest tremor, rigidity) [4, 5], PD is characterized by several interindividual non-motor symptoms (NMS) [6, 7]. Among the most prevalent NMS in PD are cognitive dysfunctions [8–10] including mild cognitive impairment (PD-MCI) and dementia (PDD) [11, 12]. Studies indicate that approximately 30–40% of people with PD experience cognitive impairment, such as PD-MCI [13, 14], with up to 32% already showing signs at diagnosis [14, 15]. Furthermore, studies indicate that the point prevalence of PDD in people with PD is up to 30%, and that up to 80% of people with PD develop PDD over the disease course [16–18]. Notably, cognitive impairment not only impacts the quality of life (QoL) of people with PD and their relatives [19–21] but also increases mortality rates [22] and carries significant health-economic consequences [23, 24]. To date, pharmacological treatments for cognitive impairment in PD are limited, associated with side effects [25, 26] and warrant careful consideration due to the polypharmacy already associated with PD [27, 28]. Hence, alongside pharmacological approaches, considerable efforts are underway to develop non-pharmacological interventions, such as physical exercise or cognitive interventions (e.g., cognitive training [CT]) to prevent and treat cognitive dysfunction in people with PD [26].

CT refers to standardized paper-and-pencil or computerized tasks aimed at enhancing cognitive functioning by targeting single or multiple cognitive domains (e.g., memory, attention, executive function, visuocognition, and language) through structured teaching strategies or guided practice [29, 30]. Previous research has yielded promising results regarding the effectiveness of CT among people with PD with no or slight cognitive impairment. For instance, one meta-analysis demonstrated improvements in overall cognition (*g* = 0.23, 95% *CI* 0.014–0.44) and also in specific cognitive functions, i.e., in executive functions (*g* = 0.30, 95% *CI* 0.01–0.58), working memory (*g* = 0.62, 95% *CI* 0.25–0.99), and processing speed (*g* = 0.31, 95% *CI* 0.01–0.61) [29]. Another meta-analysis also found significant effects of CT on cognition, specifically for executive functions (*g* = 0.51, 95% *CI* 0.16–0.85), working memory (*g* = 0.29, 95% *CI* 0.04–0.53), and memory (*g* = 0.35, 95% *CI* 0.03–0.66) [31]. Additionally, a systematic review [32] reported on positive effects of CT not only on cognitive outcomes but also on noncognitive parameters (e.g., depressive symptoms [*d* = 0.62], activities of daily living [ADL; *d* = 1.02], anxiety [*g* = 0.50]), although findings on noncognitive aspects remain inconsistent [33–35]. However, contradictory evidence on CT effectiveness has emerged from a recent Cochrane review and meta-analysis, which found no beneficial effect of CT on cognition in people with PD-MCI or PDD [30]. The authors concluded that the limited number of included studies (*n* = 7) and the heterogeneity of research designs, PD populations, and CT implementation strategies within these studies constrain the evidence derived from this analysis. They highlighted the potential of CT interventions, noting high adherence rates (up to 92%) among individuals with PD and the limited pharmacological options for treating cognitive dysfunction, underscoring the necessity for comprehensive large-scale trials to investigate the effectiveness of CT in PD [30].

Along with the call for trials with larger samples assessing CT in PD comes a need to explore CT feasibility, acceptability, and effectiveness across all stages of PD. Given that cognitive impairment is prone to evolve throughout disease progression [13, 14, 36], it is crucial to evaluate the feasibility and effectiveness of CT in both early and advanced PD stages [12]. Achieving this entails incorporating various levels of disease severity and cognitive impairment into studies [37]. Currently, most studies predominantly assess the effects of CT in PD based on the degree of cognitive impairment; this means they focus on people with PD without cognitive impairment, with PD-MCI [32, 34, 38–40], and very rarely with PDD [30, 41]. Within these studies, CT, specifically computerized CT, seems to be feasible for and accepted by people with PD [42–44]. By focusing on cognitive metrics, however, these studies overlook inclusion criteria along other disease dimensions, such as the severity of motor symptoms. Yet, different stages of motor symptom severity pose diverse challenges for people with PD in terms of disease-related complications, medical treatment, and functional and affective impairments [45–47]. These circumstances could directly and indirectly influence CT feasibility and benefits (e.g., motivation to conduct CT, motor skills to perform CT, and responsiveness to CT).

So far, few studies on CT have included people with PD according to their motor symptom severity [29, 33]; furthermore, these studies only included participants with mild to moderate motor disease stages. Studies on more advanced motor PD stages, targeting those with PD who face a heightened susceptibility to developing cognitive impairment and dementia during disease progression [48] but do not show dementia symptoms, remain scarce. Therefore, the goal of the current study is to address these research gaps and substantially contribute to a more comprehensive care of people with PD, specifically those in more advanced stages of the disease.

Next to CT efficacy, feasibility, and acceptability, this study also seeks to provide exploratory analyses of possible predictors of CT responsiveness. Current studies indicate that cognitive baseline performance might be one of the most prominent CT predictors [38, 41, 49, 50]; other factors (e.g., sociodemographic, clinical, or (neuro)psychological) may also be relevant, but the body of literature is still inconsistent [51–53]. Determining who benefits most from CT can further help to identify an individualized, personal medicine approach that specifically targets the needs of individuals with PD, therefore complementing the previous two research goals.

### Objectives {7}

Based on a hybrid type 1 clinical trial design [54], this study has three objectives. The first is to assess the short- and long-term effects of a 5-week digital CT intervention (“HeadApp/NEUROvitalis Digital” [55]) in people with advanced PD on global cognitive functions, with the Montréal Cognitive Assessment (MoCA) [56] as the primary outcome, and other cognitive, motor, and (neuro)psychological variables as secondary outcomes (e.g., specific cognitive functions, depressive symptoms, and severity of motor symptoms). It is expected that CT will improve global cognition and other cognitive and noncognitive functions, both in the short term and over a 3-month follow-up period. The second objective is to examine the feasibility and acceptability of the CT. Specifically, it is hypothesized that the CT intervention is feasible in terms of adherence to the training schedule, completion of training days, and technical handling and is acceptable in terms of participant motivation, satisfaction, and integration of CT into daily life. Finally, the study seeks to explore and identify possible predictors of CT responsiveness, including sociodemographic factors (e.g., age, sex, education), motor (e.g., severity of motor symptoms), and cognitive and (neuro)psychological factors (e.g., cognitive baseline level, self-efficacy, and depressive symptoms).

### Trial design {8}

The study is an ongoing monocentric, single-blinded, two-armed, superiority randomized controlled trial (RCT) with one group of participants (experimental group, EG) receiving a structured digital CT over 5 weeks (four times per week for 45 min) and the other group being a passive wait-list control group (control group, CG), receiving care as usual. In addition to CT, participants in the EG receive access to complementary psychoeducational videos on cognitive health. The study follows a parallel group design. Participants are allocated in a 1:1 ratio to EG and CG. After study completion, the CG will also receive access to CT and psychoeducational videos for ethical reasons. Following good clinical practice, all data will be collected and analyzed in a standardized manner. This protocol adheres to the “Standard Protocol Items: Recommendations for Interventional Trials” (SPIRIT) guidelines.

## Methods: participants, interventions, and outcomes

### Study setting {9}

The study takes place in Germany. The primary study site is the Department of Medical Psychology | Neuropsychology and Gender Studies of the Faculty of Medicine and University Hospital Cologne of the University of Cologne in Cologne, Germany. Participants can complete the digital CT remotely from home. Neuropsychological assessments pre- and post-CT, as well as the 3-month follow-up (FU), take place at the Department of Medical Psychology | Neuropsychology and Gender Studies in Cologne, Germany, at locations specifically leased for assessments outside of Cologne, at participants’ homes, or potentially at supporting research clinics in Germany.

### Eligibility criteria {10}

To be included, participants must be diagnosed with idiopathic PD according to UK Brain Bank Criteria [57] and meet the criteria for advanced PD, defined as either meeting at least one of the established 5-2-1 criteria (five intakes of levodopa/day, 2 h of OFF time/day, and/or 1 h of troublesome dyskinesia/day) [58, 59] according to self-report or receiving pump therapy (i.e., intrajejunal levodopa pump [Duodopa, Lecigon, or subcutaneous Produodopa] or s.c. apomorphine pump [e.g., APO-go]). Participants who underwent deep brain stimulation (DBS) also have to fulfill the 5-2-1 criteria. Additionally, participants should have age-appropriate cognition/no cognitive impairment or mild cognitive impairment (PD-MCI) according to level 1 diagnosis (*MoCA* ≥ 21 points) [60] and maintain stable medication for 4-week pre-CT and through baseline and post-test. Participants, of any gender, must be 18 years of age or older, proficient in the German language, and have access to a computer, notebook, or tablet with Internet access. Exclusion criteria include a level 1 diagnosis of dementia (PDD; *MoCA* < 21 points) [60], severe depression (Beck Depression Inventory [BDI-II] ≥ 29 points) [61], epilepsy or other conditions with seizure-like manifestations and/or disorders of consciousness (ICD-10 G40), and any neurological, psychiatric, or acutely life-threatening disease that could impact cognition (according to a doctor’s letter or self-report).

### Who will take informed consent? {26a}

Written informed consent is collected at the beginning of the baseline assessment by trained research fellows. Capacity to give informed consent is assessed in accordance with Good Clinical Practice [62] and local ethical standards and follows the established principles (i.e., understanding, appreciating, reasoning, communicating) [63]. Participants receive a simple-language version of the study information and consent form prior to their baseline assessment (via e-mail/post) and again in printed form at the beginning of the baseline assessment to ensure they have sufficient time to review the material. The research fellows provide explanations as needed and answer all questions. Participants keep a copy of the consent documents and study information and are encouraged to contact the study team with any subsequent questions. Participants who lack capacity to give informed consent are not enrolled. Should a participant lose capacity during the study, procedures will follow local ethical and legal requirements. If necessary, the participant’s legal representative will be informed, and continued participation will only occur with proxy consent and ethics committee approval. Ongoing monitoring of cognitive and functional status by site investigators allows timely identification and reassessment should any concerns about consent capacity arise.

### Additional consent provisions for collection and use of participant data and biological specimens {26b}

This study does not rely on additional consent provisions.

## Interventions

### Explanation for the choice of comparators {6b}

Comparators were chosen to closely reflect the current clinical routine (see Sect. "Intervention description {11a}").

### Intervention description {11a}

#### Experimental group

Participants engage in a 5-week training schedule using the scientifically based and standardized CT “HeadApp/NEUROvitalis Digital” [55], a class 1 medical device for the prevention and therapy of cognitive dysfunctions. The CT “HeadApp/NEUROvitalis Digital” is based on the pen-and-paper NEUROvitalis program [64], an evidence-based multidomain intervention developed for cognitive rehabilitation in older adults and neurological populations (e.g., PD). The analogue NEUROvitalis program has demonstrated efficacy and high user acceptance in several RCTs, including people with PD [65–67]. The digital version used in this study preserves the structure and cognitive-domain coverage of the original program while allowing home-based, adaptive training and automated performance tracking. Participants can access CT remotely and free of charge during study participation. For each participant, CT is supervised by a single member of the study team (author [name]).

Although the CT was conceptualized without specifically targeting PD, a CT schedule considering the specific cognitive profile of people with PD was developed for this study (i.e., structured rather than unstructured CT incorporating PD-relevant domains, such as working memory, memory, and executive functions [65, 66, 68]). Specifically, the structured CT schedule consists of five working memory exercises and five exercises targeting various cognitive functions: episodic memory, executive function, attention, visuocognition, and language (Fig. 1). It was specifically designed for this study and implemented into the CT program, maintaining a balanced and fixed order of exercises throughout, which participants and the study team cannot alter during the study (Table 1). The schedule consists of 20 training days to be completed over the 5-week training period. Participants are instructed to train four times per week (i.e., 4 days) for 45 min per training day, equaling 900 min in total. A training day consists of a set of three successive exercises targeting different cognitive domains (15 min each) in a prescribed order. Training frequency and duration are in accordance with previous studies on CT in PD [65, 68].

**Fig. 1 Fig1:**
[figure not shown]
Overview of the 10 cognitive training exercises of the “HeadApp/NEUROvitalis Digital” program

To seamlessly incorporate the CT schedule into participants’ daily lives and accommodate symptom fluctuations or other daily activities, participants can flexibly choose their training days on a day-to-day basis. Once participants access the CT website, they are led to the home screen of the CT showing the first of three exercises for the current training day. Each new day the CT website is accessed, a new training day is unlocked, and the set of three exercises for the day is accessible successively within that day. During CT, participants may take breaks within an exercise (via a pause button) and between the exercises (before starting the next exercise) or may discontinue an exercise. In case of the discontinuation of an exercise, CT automatically guides participants back to the home screen, where they can then start the next scheduled exercise. After the completion of all three exercises, a notification appears on the home screen of the CT stating that no further exercises are scheduled for this day and inviting participants to return another day.

Participants are advised by the study team to complete all three scheduled exercises for a specific training day on time, i.e., until midnight of that same day. They are also instructed that they may take breaks between exercises and return to the CT later that same day. However, in the case where not all scheduled exercises can be completed within one training day, the non-completed exercises of that training day cannot be revisited another day. Instead, the CT program automatically transitions to the next training day featuring the next set of three exercises regardless of whether all exercises of the previous training day have been completed. Therefore, once the first exercise of a training day is started, participants have until midnight to complete the scheduled three exercises; otherwise, these exercises will no longer be accessible. This process is repeated for all 20 scheduled training days.

As previous research has shown that the combination of CT with psychoeducation has proven to be particularly effective [44], in addition to CT, participants receive access to 18 psychoeducational videos (6–19 min) covering information on cognitive health and related lifestyle factors (i.e., information on physical exercise, nutrition, cognitive and social activity, and further risk and protective factors related to cognitive decline) as well as memory strategies (Table 1). The video content was developed by senior neuropsychologists and gerontologists (including authors [name] and [name]). The video production was operated by an external production company commissioned by the HeadApp/NEUROvitalis Digital company, HelferApp GmbH. For this study, video access is provided via a link sent to participants by email as the videos are currently not yet integrated into the CT program (but will be in the future). All videos can be rewatched via the link at any time for the duration of the study. Watching the videos is voluntary, but participants receive a suggestion on how to combine the CT schedule and videos. They receive a CT checklist (to be checked off by the participants) listing all 20 training days (from 1 to 20) combined with the title of 1 of the 18 psychoeducational videos (Table 1).

**Table 1 Tab1:**
[figure not shown]
Overview of the cognitive training schedule and psychoeducational videos

The legend of the symbols for the training tasks can be derived from Fig. 1

#### Control group

To closely reflect clinical routine, participants of the CG continue their everyday life and care as usual after the baseline assessment. After a 5-week waiting period, participants complete the post-test in week 7 and the FU assessment at week 19. Following their FU assessment, participants receive 6 months of free-of-charge access to the CT program, including the CT schedule and the psychoeducational videos.

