## Data collection and management

### Plans for assessment and collection of outcomes {18a}

#### Collection of outcomes

In total, participants will undergo three in-person neuropsychological assessments at baseline, post-test, and 3-month FU (Fig. 2). An overview of all assessments is presented in Table 2. All assessments are conducted in German by experienced research fellows or trained medicine or psychology student assistants. In general, demographic and clinical data (e.g., age, sex, PD duration, concomitant diseases, possible DBS surgery) as well as cognitive reserve measured by the Lifetime of Experiences Questionnaire (LEQ) [72, 73] are collected at baseline only. To control for stable medication treatment, all medication is listed and documented at the beginning of each assessment. This is followed by the neuropsychological assessment. An elaborate test battery with established psychometric instruments was set up to cover cognitive, motor, and further (neuro)psychological outcomes, which may be related to a CT effect. Regarding cognition, at least two tests per cognitive domain are used to allow a level 2 diagnosis of PD-MCI and the exclusion of PDD [103]. Additionally, participants undergo a short motor examination to assess motor outcomes (e.g., severity of motor symptoms, dual-task performance). Short breaks are administered during the assessment as needed. At the end of each neuropsychological assessment, several self-rating questionnaires are handed out to participants to fill out at home and return in a provided pre-addressed, stamped envelope. To assess CT feasibility and acceptability, participants of the EG receive a pen-and-paper CT diary at the end of their baseline neuropsychological assessment. Additionally, technical CT data will be used to assess CT feasibility. The following sections provide an overview of all outcome measures.

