#### Secondary outcomes: further non-motor outcomes

Lastly, several other non-motor outcomes are examined, i.e., health-related QoL, self-efficacy, ADL, and non-motor symptoms, using the Parkinson’s Disease Questionnaire (PDQ-39) [98, 99], the Self-Efficacy Scale (Selbstwirksamkeitserwartung [SWE]) [100], the Bayer Activities of Daily Living Scale (B-ADL) [101] and the Non-Motor Symptoms Questionnaire (NMSQ) [102], respectively.

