## Statistical methods

### Statistical methods for primary and secondary outcomes {20a}

The primary analysis is according to the intention to treat, with no exclusions. The change from baseline in the primary outcome MoCA is analyzed by a linear mixed model for repeated measures (MMRM) with fixed effects for baseline, group, time, and group × time interaction (ARH1-structured variance–covariance matrix over time). The primary comparison at T1 (week 9) is based on a pairwise contrast of estimated marginal means with a 95% confidence interval. Secondary outcomes (i.e., further timepoints and measures) are analyzed along the same line, however from an exploratory viewpoint only; thus, no multiplicity adjustment is required. Where available, observed changes will also be interpreted in relation to published minimally clinically important differences (MCIDs) to evaluate clinical relevance in addition to statistical significance.

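### Control-arm access is tied to the follow-up visit, but that visit's take-home questionnaires are completed later, so some T2 control self-reports may post-date access

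*Protocol article*

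**What the plan says.** Three statements in the protocol article bear on this.

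- **Release of the intervention to controls.** The Control group section says "Following their FU assessment, participants receive 6 months of free-of-charge access to the CT program", with the training schedule and the videos included. It places that assessment in time: "participants complete the post-test in week 7 and the FU assessment at week 19". The Trial design section words the release differently: "After study completion, the CG will also receive access to CT and psychoeducational videos for ethical reasons".
- **What the follow-up assessment is.** Under Collection of outcomes, "participants will undergo three in-person neuropsychological assessments at baseline, post-test, and 3-month FU".
- **How self-ratings are collected.** The same section says that at the end of each of these visits "several self-rating questionnaires are handed out to participants to fill out at home and return in a provided pre-addressed, stamped envelope". It gives no return deadline and does not say that a completion date is recorded.

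On the standing of these outcomes, the Statistical methods section says "Secondary outcomes (i.e., further timepoints and measures) are analyzed along the same line, however from an exploratory viewpoint only". The primary comparison is MoCA at T1.

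**The concern.** The stated trigger for giving controls the intervention is the visit. The T2 self-report data for the same person come into existence only later, at home. If access arrives in between, the control answers as someone who has received the programme and videos, not as someone on usual care alone.

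The exposure lies in one arm only, since the experimental group meets no new treatment at T2. Participants know their allocation and the measures are self-ratings, so knowing that access has begun could matter even before any training is done. The videos run 6 to 19 minutes each and cover cognitive health and memory strategies, so some exposure is possible within days.

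At stake is the T2 between-group contrast on the take-home scales. It is part of the evidence for the Objectives section's expectation that noncognitive benefits extend over the 3-month follow-up.

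**Working it through.** **Order of events.** The plan states no figure on this point, so the check is mainly a comparison of sections.

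1. The follow-up assessment is an in-person visit at week 19.
2. Take-home questionnaires are handed over at the end of that visit, so they are unanswered when the participant leaves.
3. Under the Control group section, access comes after the follow-up assessment, with no interval given. Under the Trial design section it comes after study completion, undefined for the individual.
4. No rule elsewhere closes the gap:
   - The Participant timeline and Implementation sections do not link access to the forms.
   - Reimbursement in the retention section depends on completed neuropsychological assessments, not on returned forms.
   - The per-protocol set asks for valid assessments at T0, T1 and T2 and keeps all controls, with no rule on questionnaire timing.
   - Reference-based imputation addresses missing values, not values observed after access.

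The text therefore permits, but does not require, the order visit, access, questionnaire.

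**What is affected.** The affected measures are the take-home self-ratings at T2 in controls. The contents of Table 2 are not visible, so which scales go home cannot be read off. Quality of life, self-efficacy, daily living and non-motor symptoms are candidates. The BDI-II is less clear: at baseline the examiner administers and scores it during the visit, and its handling at T2 is not stated.

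**Illustration of size (assumed inputs).** Let f be the share of controls who answer after access and g the fraction of the full effect they have gained by then. The contrast becomes d(1 − f·g). The documents give neither f nor g.

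A guide to g comes from the dose. The course is 20 training days at four per week. A delay of a few days allows perhaps 2 to 3 sessions, which is 2/20 = 10% to 3/20 = 15% of the course. A value of g = 0.25 would correspond to 5 of 20 days, more than a week of training. This treats gain as proportional to dose, which is itself an assumption.

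For scale only, take d = 0.5 and 63 per arm (140 × 0.9 = 126, halved), with a two-sided 5% t-test. The d is borrowed from the sample-size section, where it refers to global cognition. At d = 0.5 the same test needs 64 per arm for 80% power, which reproduces the plan's figure; the present point does not depend on that figure.

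| f | g | shrinkage f·g | contrast d(1 − f·g) | power |
|---|---|---|---|---|
| 0 | – | 0 | 0.500 | 0.795 |
| 0.25 | 0.10 | 2.5% | 0.4875 | 0.775 |
| 0.50 | 0.10 | 5% | 0.475 | 0.753 |
| 1.00 | 0.10 | 10% | 0.450 | 0.707 |
| 0.50 | 0.25 | 12.5% | 0.4375 | 0.683 |

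The table covers dilution by training gain only. A reaction to receiving access could shift ratings either way and is not captured.

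**The case against.** The best case against has four parts.

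- **The text does not say that access is immediate.** It says only that access follows the assessment. Study completion in the Trial design section can be read as the point at which the individual has finished, forms included; the retention section uses a similar phrase for individual reimbursement. The follow-up assessment might even be meant to include its questionnaires. On either reading the problem does not arise.
- **This is a condensed article.** It refers to standard operating procedures for data collection that are not shown. One unblinded team member handles training set-up and keeps a monitoring list, so access need not be given at the visit.
- **The dose gained in a few days is small.**
- **The outcomes are exploratory.**

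Most of this stands. It rules out the stronger reading that controls actually cross over at the week-19 visit: the documents show only that they may have access before answering. It also rules out inferring a large attenuation of the T2 effects. That would need controls to gain much of a 5-week course before posting their forms, and nothing in the documents supports it.

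What the objection does not remove is that the article states a release trigger, gives two versions of it, and ties neither explicitly to the questionnaires. This is a trigger in the wrong place relative to data collection, not merely a detail left out.

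**Conclusion.** The point holds as a minor one. As written, a control may complete the T2 take-home questionnaires after gaining the training and videos, so those values may not represent usual care. The conclusion rests on reading the follow-up assessment as the in-person visit, which is how Collection of outcomes describes it, and on the absence of any stated link between access and form return.

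The size cannot be determined from the documents. If forms come back within days it is probably at the low end of the illustration; training gains would pull the contrast towards no difference. A reader might infer that the trial's efficacy result, or its whole follow-up, is compromised. That is not supported: the primary MoCA comparison at T1 precedes any control access, and examiner-administered tests at T2 are done at the visit itself.

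**What to change.** **Controls not yet through T2.** Align the Trial design and Control group sections on one trigger: access is released once the completed T2 questionnaires have been received. Alternatively, have the questionnaires completed before access is given. Set a fixed cut-off after which non-returners receive access anyway, and flag any form that arrives later. Record the completion date on each form.

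**Controls already past T2.** Compare each form's completion date with the access date, using the receipt date where no completion date was recorded. Receipt is later than completion, so this substitute errs towards flagging too many forms. Run a sensitivity analysis of the T2 take-home outcomes that excludes forms completed after access, and keep the analysis of all forms alongside it, because late returners may differ from the rest.

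**Cost.** One sentence in the control-group procedure, handled by the team member who already manages access, and a slightly longer wait for controls. Recruitment was expected to end with 2025, so the new trigger can reach only late-enrolled controls. For the others the date comparison is the remedy, and it depends on which dates were kept.
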